### 12.3.2 Secondary efficacy analysis.

The combined cholesterol-lowering effect of treatment with *Plantago ovata husk* and statins to achieve the therapeutic objective will be studied. The proportion of successes, i.e. the patients in whom plasma LDL-C concentrations are below 130 mg/dl following combined treatment of *Plantago ovata husk* and statins will be calculated for each treatment.

The significance of the differences between these proportions will be evaluated using the chi-squares test. The null hypothesis considered will be that the proportion of success is the same in the two treatments for a two-tailed significance level of 0.05.

The effect of the treatment of *Plantago ovata* husk fibre on blood pressure will be evaluated by analytical procedures equivalent to those conducted to evaluate the effect of *Plantago ovata* husk fibre on plasma LDL-C concentration.

The effect of the combination of statins with *Plantago ovata* husk on blood pressure will be evaluated by analytical procedures equivalent to those conducted to evaluate the effect of the combination of statins and *Plantago ovata* husk on plasma LDL-C concentration.

The effect of the polymorphisms of apolipoprotein E, the cholesterol ester transfer protein (CETP), apolipoprotein A-V and the FABP 2 on the response in plasma lipid concentrations will be made by adjusting multiple regression models over the difference in plasma LDL-C concentrations between visits.

Furthermore, possible variations in the effects of the soluble fibre and the statins according to the characteristics at the beginning of the study, LDL-C level, gender or BMI will be studied.

A multiple linear regression model will be adjusted over the difference in the plasma LDL-C concentrations between visit S8 and visit S0, where the treatment carried out and the endpoints of age, gender, BMI, or LDL-C level at visit S0 will be used as covariates.

A multiple linear regression model will be adjusted over the success proportion, i.e. patients in whom plasma LDL-C concentrations are below 130 mg/dl following the combined treatment of *Plantago ovata* husk and statins, where the treatment carried out and the endpoints of age, gender, BMI or level of LDL-C at visit S0 will be used as covariates.

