#### **Secondary endpoint**

- To study the combined cholesterol-lowering effect of treatment with *Plantago ovata* husk and statins to achieve the therapeutic objective.
- To analyse the effect of *Plantago ovata* husk fibre on blood pressure.
- To study the effect of the combination of statins with *Plantago ovata* husk on blood pressure.
- To evaluate whether the response on plasma lipids is modulated by the polymorphisms of apolipoprotein E, cholesterol ester transfer protein (CETP), apolipoprotein A-V and FABP 2.
- Furthermore, possible variations of the effects of the soluble fibre and the statins according to the characteristics at the beginning of the study, LDL-C level, gender or BMI will be studied.

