| $e_{it}$                | indicates residual error, where $e_{it} \sim N(0, \sigma_e^2)$                                                                               |

In order to study other variables at other post-baseline visits, when necessary, an ANCOVA model will be made for each one, analogous to that described above. The baseline homogeneity will be evaluated using a Student's *t* test for independent data.

The variation in the LDL-C concentrations for week 8 to week 16, will be measured by way of intragroup analysis using analysis methods for repeat measurements.

The level of statistical significance will be established at 0.05 bilateral.

The evaluation of the continuous secondary efficacy endpoints will be analogous with the previously described ANCOVA for the primary endpoint. The continuous secondary endpoints to be analysed are described below:

- Weight and blood pressure
- Total cholesterol, triglycerides, HDL cholesterol, apolipoproteins (apo) B-100 and A-1 and lipoprotein (a).
- The oxidation markers: alpha tocopherol and gamma tocopherol in LDL, resistance of LDL to oxidation (lag time), LDL oxidation "in vivo" and lipid lipoperoxides.
- The inflammation markers: IL-1beta, interleukin-6, TNF-alpha, amyloid-A, high sensitivity C-reactive protein, fibrinogen, leukocytes.

- The indicators of antithrombotic activity: folic acid, homocysteine, plasminogen activator inhibitor (PAI-1).
- The individual response to the plasma lipids and their modulation by apolipoprotein E polymorphisms, cholesterol ester transport protein (CETP), apolipoprotein A-V, FABP 2, ABCG5 and ABCG8, fibrinogen, fibrinogen activator inhibitor, angiotensin converting enzyme and other polymorphisms which might describe their involvement in the development of cardiovascular diseases.
- Fasting complement component 3 (C3)
- Mannose-binding lectin (MBL) activity
- Remnant-like particle cholesterol concentration (RLP-C)
- Parameters of cholesterol absorption and synthesis: plant sterols (campesterol and beta-sitosterol, reflecting cholesterol absorption) and lathosterol (reflecting cholesterol synthesis)
- Determination of atherogenic apo B-containing particles (VLDL, IDL and LDL subclasses),
- HDL particle phenotype and HDL particle composition
- Cholesterol ester transfer protein activity

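### The regressions in 12.3.2 that are meant to show whether the treatment effect varies with baseline LDL-C, gender or BMI name no treatment-by-covariate term, and linear regression is named for a yes/no success outcome

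*Protocol*

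**What the plan says.** Section 4.2 lists two secondary objectives about effect modification. One is "To evaluate whether the response on plasma lipids is modulated by the polymorphisms of apolipoprotein E" and three further genes. The other concerns variation in the fibre and statin effects by baseline characteristics. Section 12.3.2 repeats the second aim, with BMI as one more factor after those quoted here: "possible variations in the effects of the soluble fibre and the statins according to the characteristics at the beginning of the study, LDL-C level, gender".

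The analyses that bear on these aims are:

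- **S8−S0 change in LDL-C (12.3.2).** Multiple linear regression, "where the treatment carried out and the endpoints of age, gender, BMI, or LDL-C level at visit S0 will be used as covariates".
- **Success after combined treatment (12.3.2).** "A multiple linear regression model will be adjusted over the success proportion", with treatment and the same four factors as covariates. Success means LDL-C below 130 mg/dl. Earlier in the same section the arms are compared on this outcome: "The significance of the differences between these proportions will be evaluated using the chi-squares test".
- **Genotype (12.3.2).** The analysis "will be made by adjusting multiple regression models over the difference in plasma LDL-C concentrations between visits". No model terms are given.
- **Subgroups (12.3.4).** If enough patients are treated, two-way ANOVAs of the S8−S0 change by treatment and gender, and by treatment and baseline LDL-C band (130–149, 150–169, 170–189), with Bonferroni correction of post-hoc tests.

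Section 12 mentions neither an interaction term nor logistic regression.

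**The concern.** Whether a treatment effect varies with BMI is a question about the product of treatment and BMI. If both enter only as covariates, the model holds the treatment effect constant over BMI. The BMI coefficient then says whether BMI predicts LDL-C change in the two arms together. A reader could take a significant BMI or gender coefficient as evidence that fibre works differently in those patients, which it is not. The risk is real here because section 8.3.2 puts all patients on a stricter diet after S0, and response to that diet may itself depend on patient characteristics in both arms.

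The second difficulty is the success model. Each patient either is or is not below 130 mg/dl. Ordinary linear regression on such an outcome can give fitted probabilities below 0 or above 1, and its usual standard errors assume a constant variance that a yes/no outcome does not have.

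At stake are secondary objectives: the trial would collect the data to address them and then fit models that cannot.

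**Working it through.** **1. The plan's own figures (section 6.3).** With a difference of 7.5 mg/dl, SD 20, two-sided alpha 0.05 and power 80%:

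n per group = 2 × (1.960 + 0.842)² × 20² / 7.5² = 111.6, rounded up to 112, as stated. Allowing for 15% losses, 112/0.85 gives 132 per group, or 264 in total, close to the stated 270. For the statin phase the same method gives 110 and 97 against the stated 111 and 98. Inflation then gives 111/0.85/0.9 = 145.1 and 98/0.75/0.9 = 145.2, against 145 per group. No sample-size figure is in dispute. SD 20 and the range N = 224 (2 × 112) to 290 are carried forward.

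**2. What the covariate model estimates.** As written, mean change = a + b·T + c·X, so the treatment difference is b at every value of X. With a product term, mean change = a + b·T + c·X + d·T·X, so the difference is b + d·X, and d is the variation asked about.

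Take an assumed binary modifier split 50:50, with a fibre effect of −15 in one half and 0 in the other. The covariate model estimates 0.5 × (−15) + 0.5 × 0 = −7.5 and contains no parameter for the 15 mg/dl contrast. Simulation (4,000 trials, N = 290, SD 20) agrees:

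| True difference in effect (mg/dl) | Treatment coefficient, covariates only | Product-term estimate | Rejection rate for product term |
|---|---|---|---|
| 0 | −7.6 | −0.1 | 0.06 |
| 7.5 | −7.5 | −7.6 | 0.36 |
| 15 | −7.5 | −14.9 | 0.88 |

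The covariate-only result is essentially the same in all three situations.

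**3. Which modifiers have another route.**

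- BMI: none. It is absent from 12.3.4.
- Gender and baseline LDL-C: the ANOVAs of 12.3.4. They depend on numbers, do not name the interaction, use the S8−S0 change only, and cut LDL-C into three bands. They do not reach the statin phase, although the aim includes statins.
- Genotype: a regression with unlisted terms.

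**4. Power once the product term is added.** For a binary modifier with fraction f in one category and 1:1 allocation (section 5.2), SE = 20 × √[2/(f·N/2) + 2/((1−f)·N/2)]. Power for a 7.5 mg/dl interaction is Φ(7.5/SE − 1.96) + Φ(−7.5/SE − 1.96). The interaction detectable with 80% power is 2.802 × SE.

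| N | Split | SE | Power for 7.5 | Detectable with 80% power |
|---|---|---|---|---|
| 290 | 50/50 | 4.70 | 0.36 | 13.2 |
| 290 | 20/80 | 5.87 | 0.25 | 16.5 |
| 224 | 50/50 | 5.35 | 0.29 | 15.0 |
| 224 | 20/80 | 6.68 | 0.20 | 18.7 |

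**5. Linear regression on success.** Section 6.3 implies falls to 125.6/157 = 0.80 (fibre + statin) and 136.85/161 = 0.85 (placebo + statin) of the starting value. For illustration, apply these ratios to a baseline LDL-C assumed uniform on 130–189, with normal residuals. A linear fit of success on treatment and baseline then gives:

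| Residual SD (assumed) | Range of fitted probabilities | Share of patients outside 0–1 |
|---|---|---|
| 10 | −0.22 to 1.16 | 18% |
| 15 | −0.10 to 1.05 | 7% |
| 18.5 | −0.03 to 0.98 | 2% |

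**The case against.** The strongest reply is that model terms are normally settled in the statistical analysis plan, which is not shown. That answers part of the point:

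- **Genotype.** A reader might infer that the genotype regression has main effects only. The protocol does not say so. It lists no terms, and an interaction is not excluded. A request to name the term is a clarification and not a charge of error.
- **Gender and baseline LDL-C.** A reader might infer that effect modification by these factors is not analysed at all. A two-way ANOVA with treatment as one factor normally carries the interaction, so 12.3.4 is a partial answer, within the limits set out in the working.
- **The list in 12.3.1.** It places "The individual response to the plasma lipids and their modulation by apolipoprotein E polymorphisms" among the continuous endpoints for the baseline-adjusted ANCOVA. A reader might infer that a genotype is to be given a baseline value. That is a strained reading: the response is the lipids, which do have baselines, and 12.3.2 gives the polymorphisms their own regression. It is loose drafting.
- **The success model.** A reader might infer that normal errors of constant variance are prescribed for it. That error term is stated only for the ANCOVA in 12.3.1. A linear model on a yes/no outcome can also be defended as a risk-difference model with robust standard errors, and the unadjusted comparison by chi-square suits the outcome.

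The reply does not rescue the regressions in 12.3.2 themselves. There the protocol does list the terms, directly after stating the aim, and they do not match it. Nor does it state the robust risk-difference reading of the success model.

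**Conclusion.** The point holds in this limited form. The covariate regressions fixed in 12.3.2 cannot show whether the effects of fibre or statins vary with baseline LDL-C, gender or BMI. For BMI nothing elsewhere fills the gap. For gender and baseline LDL-C only the conditional ANOVAs of 12.3.4 do, and only for the S8−S0 change. For genotype the terms are unspecified. Naming linear regression for success is a plain mismatch with a yes/no outcome, although its practical size depends on assumptions: 2% to 18% of patients with fitted values outside 0–1 in the illustration.

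It would go too far to infer that the corrected models will settle these questions. With 20–36% power for a 7.5 mg/dl interaction, a non-significant result would say little. Nor is the main conclusion of the trial at risk: the primary ANCOVA, the sample size and the chi-square comparison of success are untouched.

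The binary modifier and its splits, the baseline distribution, the application of the 0.80 and 0.85 ratios to S0 values, and the residual SDs in the success illustration are assumptions. SD 20 for the change, 7.5 mg/dl and the range of N come from section 6.3.

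**What to change.** In 12.3.2:

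1. Add treatment × BMI, treatment × gender and treatment × baseline LDL-C (continuous) to the regressions, one modifier at a time.
2. State that the genotype regression includes treatment × polymorphism, since modulation of the fibre response is the objective.
3. Report each interaction estimate with its 95% confidence interval, label these analyses exploratory, and cross-refer to 12.3.4 so that the ANOVAs and the regressions are read together.
4. For success, replace linear with logistic regression, or state that a risk-difference model with robust standard errors is intended.

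The cost is a change of wording. No new data, visits or patients are needed. The price is a set of low-powered exploratory estimates with wide intervals, which the labelling makes plain.

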### **12.3.3. Interim analyses**

No interim analyses are provided for

### **12.3.4. Subgroup analysis**

If the number of patients treated is high enough, subgroup comparisons will be conducted to evaluate whether there are changes in the values of plasma LDL-C concentrations between gender and for different initial LDL-C levels (130-149, 150-169, 170-189).

For this purpose, two-way ANOVAs will be performed [(treatment and gender) and (treatment, LDL-C start)] for the difference in plasma LDL-C concentrations between visit S8 and visit S0. The Bonferroni corrections will be taken into account for multiple post-hoc tests.

## **12.4. Analysis populations**

The statistical analysis will be performed both for intention to treat (each patient is analysed in the group he/she was assigned to at the beginning of the study regardless of whether he/she did not comply with the corresponding intervention) and by protocol, which only includes patients who complied suitably with the intervention that was assigned to them.

The safety analysis will include all the patients who received study medication; the adverse events in each treatment will be described graphically and/or numerically.

The Spanish version 11 of the statistical application package SPSS will be used for the data analysis.

A two-tailed significance of 0.05 will be considered in all statistical tests.

#### **12.4.Data management and Analysis centre**

Quintiles: will be responsible of the management of the preparation and starting of the trial, as well as the monitoring of it. As well will be take care of the data management.

Asociación Hipótesis alternativa: Will be take care of the statstical analysis and the final report, as well statistic as clinical.

# **ANNEX 1**

## **Study evaluations diagram**

## STUDY EVALUATIONS DIAGRAM VISITS

| Day / Week                      | S-2 | D-10 | D-7 | S0 | S4 | S7
(1) | S7
(2) | S8 | S12 | S15
(1) | S15
(2) | S16 |
|---------------------------------|-----|------|-----|----|----|-----------|-----------|----|-----|------------|------------|-----|
| Clinical history                | X   |      |     | X  | X  |           |           | X  | X   |            |            | X   |
| Physical Examin.                | X   |      |     | X  | X  |           |           | X  | X   |            |            | X   |
| Weight                          | X   |      |     | X  | X  |           |           | X  | X   |            |            | X   |
| Height                          | X   |      |     |    |    |           |           |    |     |            |            |     |
| BMI                             | X   |      |     | X  |    |           |           | X  |     |            |            | X   |
| Blood Pressure                  | X   |      |     | X  | X  |           |           | X  | X   |            |            | X   |
| Assessment
Physical Activity | X   |      |     |    |    |           |           | X  |     |            |            | X   |
| Informed
Consent             | X   |      |     |    |    |           |           |    |     |            |            |     |
| Lipid profile                   |     | X    | X   |    |    | X         | X         |    |     | X          | X          |     |
| Genetic
polymorphisms        |     |      | X   |    |    |           |           |    |     |            |            |     |
| Biochemistry                    |     |      | X   |    |    |           | X         |    |     |            | X          |     |
| Haemogram                       |     |      | X   |    |    |           | X         |    |     |            | X          |     |
| Minerals                        |     |      | X   |    |    |           | X         |    |     |            | X          |     |
| Vitamins                        |     |      | X   |    |    |           | X         |    |     |            | X          |     |
| Delivery of
diet record      | X   |      |     | X  | X  |           |           | X  | X   |            |            |     |
| Collection of
diet record    |     |      | X   |    | X  |           | X         |    | X   |            | X          |     |
| Collection of AEs               |     |      |     |    | X  |           |           | X  | X   |            |            | X   |
| Delivery of
medication       |     |      |     | X  | X  |           |           | X  | X   |            |            |     |
| Collection of
medication     |     |      |     |    | X  |           |           | X  | X   |            |            | X   |

# **ANNEX 2**

## **Diet evaluations diagram**

### DIET EVALUATIONS DIAGRAM

|                              | S-2 | D-10 | D-7 | S0 | S4 | S5 | S6 | S7
(1) | S7
(2) | S8 | S9 | S10 | S11 | S12 | 13 | S14 | S15
(1) | S15
(2) | S16 |
|------------------------------|-----|------|-----|----|----|----|----|-----------|-----------|----|----|-----|-----|-----|----|-----|------------|------------|-----|
| Delivery of
diet record   | x   |      |     | x  | x  |    |    |           |           | x  |    |     |     | x   |    |     |            |            |     |
| Collection of
diet record |     |      | x   |    | x  |    |    |           | x         |    |    |     |     | x   |    |     |            | x          |     |
| 24-h
reminder             |     |      |     |    |    | x  | x  | x         |           |    | x  | x   | x   |     | x  | x   | x          |            |     |

## **ANNEX 5**

### **Physical activity questionnaire**

## PHYSICAL ACTIVITY QUESTIONNAIRE

### PHYSICAL ACTIVITY AND EXERCISE

**Job / Occupation (8h) Type:** \_\_\_\_\_

- |                                                       |                          |
|-------------------------------------------------------|--------------------------|
| Almost always sitting down                            |  |
| Sitting down half the time                            |  |
| Almost always standing                                |  |
| Almost always walking, lifts,
carrying light loads |  |
| Almost always walking, lifts,
carrying heavy loads |  |
| Heavy manual work                                     |  |

**Walking / bicycle** (Not sport, mode of transport to get about, strolling, entertainment)

- |                      |                          |
|----------------------|--------------------------|
| Hardly ever          |  |
| Less than 20 min/day |  |
| 20-40 min/day        |  |
| 40-60 min/day        |  |
| 1 – 1.5 h/day        |  |
| More than 1.5 h/day  |  |

**Home / housework** (If it is not relevant, leave blank)

- |                   |                          |
|-------------------|--------------------------|
| Less than 1 h/day |  |
| 1-2 h/day         |  |
| 3-4 h/day         |  |
| 5-6 h/day         |  |
| 7-8 h/day         |  |
| More than 8h/day  |  |

**Free time** (average day)

*TV / Reading*

- |                   |                          |
|-------------------|--------------------------|
| Less than 1 h/day |  |
| 1-2 h/day         |  |
| 3-4 h/day         |  |
| 5-6 h/day         |  |
| More than 6 h/day |  |

**Exercise** (sports) **type:** \_\_\_\_\_

- |                    |                          |
|--------------------|--------------------------|
| Less than 1 h/week |  |
| 1 h/week           |  |
| 2-3 h/week         |  |
| 4-5 h/week         |  |
| More than 5 h/week |  |

How many hours a day do you sleep usually?

hours

Habits (time taken to get dressed, shave, get ready,...)

hours

## Physical activity questionnaire. Assignment of values in MET

|                                                                                        | MET values (not shown
the questionnaire) |
|----------------------------------------------------------------------------------------|---------------------------------------------|
| Job / Occupation (8h) Type: _____                                               |                                             |
| Almost always sitting down                                                             | 1.3                                         |
| Sitting down half of the time                                                          | 1.8                                         |
| Almost always standing                                                                 | 2.2                                         |
| Almost always walking, lifts,
doing a little carrying                               | 2.6                                         |
| Almost always walking, lifts,
doing a lot of carrying                               | 3.0                                         |
| Heavy manual work                                                                      | 3.9                                         |
| Walking / bicycle                                                               | 3.6                                         |
| (10') Hardly ever (0.16)                                                               |                                             |
| (15') Less than 20 min / day (0.25)                                                    |                                             |
| (30') 20-40 min./day (0.50)                                                            |                                             |
| (50') 40-60 min./day (0.83)                                                            |                                             |
| (75') 1 – 1.5 h/day (1.15)                                                             |                                             |
| (100') More than 1.5 h/day (1.6)                                                       |                                             |
| Home / Housework                                                                | 2.5                                         |
| (0.5h) Less than 1 h/day                                                               |                                             |
| (1.5h) 1-2 h/day                                                                       |                                             |
| (3.5h) 3 -4 h/day                                                                      |                                             |
| (5.5.h) 5-6 h/day                                                                      |                                             |
| (7.5h) 7-8 h/day                                                                       |                                             |
| (10h) More than 8h/day                                                                 |                                             |
| Free time                                                                       | 1.2                                         |
| TV / Reading                                                                    |                                             |
| (0.5h) Less than 1 h/day                                                               |                                             |
| (1.5h) 1-2 h/day                                                                       |                                             |
| (3.5 h) 3-4 h/day                                                                      |                                             |
| (5.5h) 5-6 h/day                                                                       |                                             |
| (8h) More than 6 h/day                                                                 |                                             |
| Exercise                                                                        | 5.0                                         |
| (0.5h) Less than 1 h/week                                                              |                                             |
| (1h) 1 h/week                                                                          |                                             |
| (2.5h) 2-3 h/week                                                                      |                                             |
| (4.5h) 4-5 h/week                                                                      |                                             |
| (6h) More than 5 h/week                                                                |                                             |
| How many hours a day do you sleep
usually?  hours               | 0.9                                         |
| Habits (time taken to get dressed,
Shave, get ready,...)  hours | 2.0                                         |

\*MET (metabolic equivalents), Kcal = METxKg

